### Study population, cluster eligibility, and cluster recruitment

Eligible PCCs were those with the highest relative CNI in Region Stockholm. A lower CNI limit was set at 1.0 which represents the median value. First, the managers from the 50 PCCs with the highest relative CNI in the region were invited to a meeting where they were informed about the trial and had the opportunity to ask questions. After that, they had 14 days to decide whether they would like to sign up their PCC for participation. Because we did not reach the recruitment goal of 30 PCCs within these 14 days, the recruitment procedure was repeated with an additional 32 PCCs. Thus, a total of 82 PCCs were invited, and by 19 May 2023, the recruitment of PCCs was completed, resulting in a total of 31 PCCs that agreed to participate. One additional PCC informed us with their agreement to participate after the 14-day deadline was completed (31 October 2023) and after the randomization (see description below) of the 31 PCCs. However, the steering committee decided to include this PCC and randomize it individually. The relative CNI for the 32 randomized PCCs range from 2.83 to 1.07. A flowchart of cluster eligibility, recruitment, and randomization is presented in Fig. 1.

**Fig. 1 Fig1:**
[figure not shown]
Flowchart of cluster eligibility, recruitment, and randomization

### Randomization and blinding

A matched-pair cluster randomization was performed using the R Statistical Software 4.1.3 [25], employing the *rbinom* function to generate computer-generated random numbers. The underlying code is available in Additional file 1, and the procedure was as follows. First, participating PCCs were matched based on their CNI by pairing 1:1 adjacent values of CNI, after ranking them from highest to lowest. The difference between adjacent values was judged in most cases as very small (i.e., lower than 2%). Thereafter, randomization was conducted within each matched pair. In one case, three PCCs were matched together due to the uneven number of PCCs. Out of the 31 PCCs included in the first step of recruitment, 16 were randomly allocated to HDI and 15to OS. The additional PCC that was included in a second step was randomly allocated to OS. Thus, a total of 16 PCCs were allocated to HDI and 16 to OS.

The statistician ([name]) who performed the randomization, and who will perform the outcome analysis, was blinded to the meaning of the computer-generated random numbers which determined the allocation of clusters to either HDI or OS. However, given the open-label and pragmatic design, participants and outcome assessors will not be blinded. As such, emergency blinding will not occur in this trial.

### Recruitment of participants, eligibility criteria, and informed consent

Patients aged 50–59 years old who are enlisted at the participating PCCs will be considered eligible for invitation to participate in the trial. Each of the PCCs will be asked to invite and enroll patients until they have reached *n* = 100 participants. For PCCs randomized to HDI, a healthcare professional (registered nurse or general practitioner) from the PCC will send a letter by mail to eligible patients, providing brief information about the intervention and a scheduled date and time for a phone call. During the phone call, the healthcare professional will provide more information about the intervention and the potential participant will have the opportunity to ask questions. Previous research indicates that this approach (information by ordinary mail followed by a phone call) could increase attendance rates compared to a mail-only invitation [26, 27]. If the patient expresses an interest in participating, an appointment for the screening and the health dialogue will be scheduled. Based on all enlisted patients, the healthcare professional will invite patients consecutively based on alphabetical order of their surnames. Patients choosing to participate will provide written informed consent and have the possibility to withdraw their participation at any time without the need to state a reason (Additional file 2). As part of the participant information and informed consent, participants are made aware that the trial is designed to evaluate how well HDI and OS can detect biological risk factors (surrogate endpoints) for T2D and CVD (target outcomes) and whether they lead to reduced risk of T2D and CVD in the long-term.

For PCCs randomized to OS, eligible patients will be identified upon scheduling an appointment at their PCC for any reason, except for those whose scheduled appointments are related to hypertension, T2D, and CVD, or acute events requiring immediate care or immediate referral. Upon scheduling the appointment, the healthcare professional (assistant nurse, registered nurse, or general practitioner) will provide brief information about the trial. Next, once the patient arrives for their visit, they will again be given information about the trial. If agreeing to participate, they will provide written informed consent and have the possibility to withdraw their participation at any time without the need to state a reason (Additional file 3). Figure 2 shows the timeline of the study, including timepoints for enrollment, allocation, and assessments, as per SPIRIT guidance.

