### Sample size

Sample size calculations were based on change in systolic blood pressure as the main outcome measure. We considered a 5-mmHg reduction in systolic blood to be clinically relevant as meta-analyses of randomized trials show that such a reduction can reduce the risk of CVD by about 10% regardless of CVD history, including among people with normal to high-normal blood pressure [22], as well as specifically in middle-aged adults [23].

Based on systolic blood pressure data in Stockholm Region that were obtained from electronic medical records, the estimated variance of systolic blood pressure levels between PCCs (clusters) was equal to 2, and the variance between subjects within PCCs (individuals) was equal to 256. These settings give rise to the underlying variance structure of the data, essential for sample sizes calculations, namely a difference of 5 mmHg in systolic blood pressure between arms (VA = 12.5), variance between clusters, (VC = 2), and variance between individuals within PCCs (VE = 256). We calculated the number of clusters, the number of individuals, and the power of the sample using various combinations of VA, VC, and VE values close to those outlined above. For each calculation, we adjusted one parameter while holding the other two constant. We used the package clusterPower version 0.7.0 [24], R Statistical Software version 4.1.3 [25], for the sample size and/or power calculations for the different variance settings.

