Accordingly, we calculated that based on 15 clusters in each arm, a minimum of 840 participants (*n* = 420 in each arm and *n* = 28 per cluster) would yield 80% power to detect a reduction of 5 mmHg systolic blood pressure in the HDI group as compared to OS. Rising power to 90% while keeping the number of clusters to 15 per arm would require a minimum of 1200 participants (*n* = 600 in each arm and *n* = 40 per cluster). Additionally, anticipating difficulties with cluster recruitment and retention, we also calculated that if the size of the cluster is increased to *n* = 69, a power of 80% would be obtained with 9 clusters per arm, and 90% power would be obtained with 11 clusters per arm. Because we expected difficulties with recruitment of PCCs and participant recruitment within PCCs, as well as subsequent attrition of the two, the goal was to recruit at least 30 PCCs (*n* = 15 in each arm) in Stockholm Region, each of which will aim to recruit *n* = 100 participants, yielding a maximum total study population of *N* = 3000.

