### Statistical analysis

Baseline characteristics in the two arms will be described by means of typical summary measures e.g., means, medians, frequencies, proportions, standard deviations, quartiles, and counts. Characteristics of dropouts will be explored in comparison to non-dropouts.

The core tool of outcome analysis will be a hierarchical model consisting of two levels, individuals and PCCs. The primary model for analyzing changes in systolic blood pressure (primary outcome), other biological risk factors, lifestyle habits, and HRQoL over 6 and 12 months will be a mixed-effects generalized linear model (GLM) to capture variability between and within PCCs. Following the GLM framework, the assumptions concerning the underlying probability distribution and the link function (the way the expected value of the outcome is related to a set of independent variables and their associated effects) will differ between continuous, binary, categorical, and count outcomes. In these models, the treatment effect (HDI versus OS) will be assessed using a fixed effect represented by a dummy variable at PCC level, specifying the type of treatment (HDI/OS). Together, this enables the estimation of the average treatment effect, while accounting for the hierarchical structure of the data. We will estimate unadjusted effects and effects adjusted both/either at the individual level and PCC level, e.g., adjusted for demographic characteristics, socioeconomic status, CNI level, and baseline values of the referred outcome. The analyses will be conducted on an intention-to-treat basis and will be carried out using the *glmer* function of the *lme4* package under the R platform [47]. Potential effect modification will be explored through subgroup analyses and interaction analyses considering sex, birth country, and socioeconomic characteristics. A sensitivity analysis will be conducted to assess whether the individual randomization of a single PCC introduced bias. Thus, we will perform analyzes both including and excluding this PCC. The occurrence of missing data will be dealt with accordingly.

For the assessment of T2D and CVD incidence and mortality during the extended 5 and 10 years of follow-up, we will calculate hazard ratios using a mixed-effect Cox regression model and packages *survival* and *coxme* under the R platform [48–50]. We will also calculate the number needed to treat (NNT).

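### The two arms recruit under different entry rules after randomization, and neither the unadjusted change nor adjustment for baseline SBP alone reliably removes the imbalance this can create

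*Protocol article*

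**What the plan says.** The protocol article's section on recruitment, eligibility and consent opens with one rule for the trial: "Patients aged 50–59 years old who are enlisted at the participating PCCs will be considered eligible for invitation to participate in the trial". It then gives each arm its own route.

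- **HDI:** "Based on all enlisted patients, the healthcare professional will invite patients consecutively based on alphabetical order of their surnames". No disease-related exclusion is stated.
- **OS:** patients are identified when they schedule an appointment for any reason, "except for those whose scheduled appointments are related to hypertension, T2D, and CVD, or acute events requiring immediate care or immediate referral".

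The primary outcome is change in SBP at 6 and 12 months. On the effect estimates, the Statistical analysis section says: "We will estimate unadjusted effects and effects adjusted both/either at the individual level and PCC level". Its examples of covariates are demographic characteristics, socioeconomic status, CNI level and the baseline value of the outcome. Prior diagnosis and prior medication are not among them, and neither estimate is named as primary.

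The Discussion acknowledges selection bias from unblinded recruitment after randomization, calls its direction unpredictable and commits to covariate adjustment. It does not mention that the entry rules themselves differ by arm.

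**The concern.** Cluster randomization balances the PCCs. It does not balance the people enrolled afterwards if each arm selects them differently. Here the OS exclusion names hypertension, which bears directly on the primary outcome, and the two target diseases. HDI has no counterpart to it. OS also requires the person to be seeking care, and takes the baseline reading at a visit made for another complaint. HDI takes it at a planned dialogue visit.

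If the rules produce arms with different shares of known hypertension, part of the SBP contrast reflects who was recruited. The two planned kinds of estimate can then disagree for structural reasons, and a reader would not know which to believe. Comparisons of first-time case finding, attainment of the blood pressure target, and T2D and CVD incidence would be exposed to the same difference in prior disease.

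**Working it through.** **The plan's own figure.** The Sample size section takes "a difference of 5 mmHg in systolic blood pressure between arms" and says that "the estimated variance of systolic blood pressure levels between PCCs (clusters) was equal to 2" (VC) and "the variance between subjects within PCCs (individuals) was equal to 256" (VE). It states that 15 clusters per arm of 28 "would yield 80% power to detect a reduction of 5 mmHg systolic blood pressure in the HDI group as compared to OS". With SE = √[2(VC + VE/m)/J], a t reference on 2(J − 1) df and an assumed two-sided 5% level, these inputs give SE = √[2(2 + 256/28)/15] = 1.22 and power 97.7%. The stated 80% is reproduced with both variances doubled (SE 1.72, power 80.0%), as for a change score with no baseline correlation. The discrepancy is conservative and does not affect this point. VC and VE are reused below.

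**Inputs the protocol does not give (assumed).** Share with known hypertension p = 0.30; share of these lost to OS through the appointment rule f = 0.5; SBP gap D = 12 mmHg; baseline to follow-up correlation ρ = 0.6. No treatment effect.

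**Step 1, imbalance (HDI minus OS).**
- Hypertensive share in OS: q = p(1 − f)/(1 − pf) = 0.15/0.85 = 0.176.
- Baseline difference: g = D(p − q) = 12 × 0.124 = 1.48 mmHg.
- Over p = 0.2–0.4, f = 0.25–1 and D = 5–15, g runs from 0.2 to 6.0 mmHg. It is zero if D = 0, that is, if known hypertension is controlled.

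**Step 2, bias if the hypertensives' SBP is stably higher.**
- The gap is present at both times, so the unadjusted change has bias 0.
- Hypertension adds between-person variance of 144 × 0.30 × 0.70 = 30.2 in HDI and 144 × 0.176 × 0.824 = 20.9 in OS, mean 25.6.
- Slope on baseline within arm = (0.6 × 256 + 25.6)/(256 + 25.6) = 0.636.
- Bias with adjustment for baseline only = 1.48 × (1 − 0.636) = +0.54 mmHg, against HDI.

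**Step 3, bias if follow-up regresses to a common mean.**
- Unadjusted change: −g(1 − ρ) = −1.48 × 0.4 = −0.59 mmHg, in favour of HDI.
- Adjusted for baseline only: 0.

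**Step 4, remedy.** Simulation under both mechanisms gave estimates within a few hundredths of a mmHg of zero when prior diagnosis was added to baseline SBP. Restricting both arms to people without the diagnosis gave the same.

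| Estimate | Stable gap | Common mean |
|---|---|---|
| Unadjusted change | 0 | −0.59 |
| Baseline SBP only | +0.54 | 0 |
| Baseline SBP + diagnosis | about 0 | about 0 |

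**Step 5, effect on error rates, common-mean case only.**
- For the unadjusted change with 16 PCCs per arm and 100 people each, SE = √[2(2/16 + 2 × 256 × 0.4/1600)] = 0.711. This assumes that VC also applies to changes.
- Baseline gaps of 2, 3 and 4 mmHg give biases of 0.8, 1.2 and 1.6 mmHg and two-sided false-positive rates of 20%, 39% and 61%.
- At 3 mmHg, ρ from 0.5 to 0.7 gives 51% to 27%.
- At 3 mmHg and ρ = 0.6, the 39% falls to 33%, 25% and 20% with 69, 40 and 28 people per PCC.
- For a gap of about 1.2 mmHg (p = 0.3, f = 0.5, D = 10), the rate is about 11% at 100 per PCC and 7% at 28.

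**The case against.** A reader might infer that the arms do differ in baseline blood pressure and that the unadjusted change is therefore biased. The protocol supports neither step. It gives no baseline SBP by arm, no hypertension prevalence and no correlation. The OS rule removes appointments, not diagnoses, so a hypertensive patient who books for another reason stays eligible. Treated hypertension may be controlled, and care-seeking or a reading taken during another complaint could raise OS values. Measurement technique is the same in both arms. Imbalance alone does not bias a change score either: in step 2 the change is unbiased and the baseline-adjusted estimate is not. All of this stands.

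It is also fair that the protocol already plans adjusted effects, lists the baseline outcome value, and commits to covariate adjustment against imbalance. Naming the primary model and its full covariate list is often left to an analysis plan, so an incomplete list is not itself a defect. Collecting incident disease implies removing prevalent cases.

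What remains is the entry rule, which this document fixes differently by arm. The stated limitation traces selection bias to lack of blinding only. Of the covariates the protocol mentions, baseline SBP is the closest to the problem, and step 2 shows it can be insufficient by itself.

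**Conclusion.** The point holds as a structural risk to comparability. The arms recruit under different rules after randomization, the difference concerns conditions tied to the primary outcome and the target diseases, and the limitations do not name it. Its direction and size cannot be determined from the protocol.

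Under the illustrative inputs, either the unadjusted change or the baseline-only adjusted estimate is off by about 0.5–0.6 mmHg, in opposite directions. That is 11–12% of the 5 mmHg target (0.54/5 and 0.59/5). If the imbalance ran the other way, the signs would reverse. The true bias could be nil.

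The 20–61% false-positive rates should not be read as a property of the trial. They need an assumed gap of 2–4 mmHg, correlation 0.6, regression to a common mean and full recruitment of 100 per PCC.

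**What to change.** 1. Make one model primary: follow-up SBP on arm within the planned mixed model, adjusted for baseline SBP, age, sex, prior hypertension, T2D or CVD diagnosis (VAL) and antihypertensive dispensing before baseline (Prescribed Drug Register). Report the unadjusted change as descriptive.
2. Add a supportive analysis restricted in both arms to participants with no prior hypertension, T2D or CVD diagnosis. Describe it as a common-population analysis. It does not replicate the OS rule, which works by appointment reason and leaves some diagnosed patients in.
3. State that the incidence analyses exclude prevalent T2D or CVD in both arms by the same register rule.
4. Name the arm-specific entry rule and the different setting of the baseline measurement among the limitations.

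**Cost.** These are changes of wording and analysis, to be settled before the data are analysed. The protocol already plans to obtain diagnoses from VAL and dispensing data at baseline, so no new data source is needed. The restricted analysis loses participants and precision. Adjustment will not remove differences due to care-seeking itself or to transiently raised OS baseline readings.

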**Fig. 2 Fig2:**
[figure not shown]
SPIRIT figure for schedule of enrollment, intervention, and assessment

Additionally, from each of the participating PCCs, we will invite healthcare professionals for an assessment of process and implementation outcomes. For PCCs randomized to HDI, we will invite the healthcare professional that has been responsible for conducting the health dialogue and possibly also the manager. For PCCs randomized to OS, we will invite all healthcare professionals who have been implementing the intervention. Those agreeing to participate will provide written informed consent and have the possibility to withdraw their participation at any time without the need to state a reason (Additional file 4), after which they will respond to a questionnaire. A selection of healthcare professionals will be invited to participate in a semi-structured interview, as described in later sections.

### Intervention descriptions

#### Health dialogue intervention (HDI)

Patients consenting to participate in the trial, and enlisted at a PCC randomized to HDI, will receive an intervention following the Swedish prevention program for lifestyle-focused health dialogues [15]. The program includes a systematic screening assessment which forms a risk profile (see below). Based on the results of the assessment and the risk profile, participants will be offered an individually oriented lifestyle-focused health dialogue. The program has been developed in Swedish primary care since the mid-1980s [13, 14], and is briefly mentioned in the National Guidelines for Prevention and Treatment of Unhealthy Lifestyle Habits, developed by the Swedish National Board of Health and Welfare [7]. The model is currently used in 13 of the 21 regions in Sweden, with an additional five regions running pilot programs or launching the program shortly. In short, the program aims to map risk factors for T2D and CVD among all individuals in certain age groups, and to provide knowledge and subsequent guidance and support behavior change with respect to lifestyle habits, including subsequent follow-ups, with the primary goal of preventing T2D and CVD [15].

The intervention will be conducted according to the following procedure. First, ahead of the scheduled health dialogue, participants will be asked to fill out a health survey. For participants with language barriers, it will be possible to fill out the survey with the assistance from an interpreter in their native language in conjunction with the forthcoming health dialogue. The survey assesses various aspects of health status and lifestyle habits, including medical history, medications, general health, mental health, heredity, living situation, quality-of-life, alcohol consumption, dietary habits, tobacco and/or nicotine use, and physical activity. Second, participants will be instructed to leave blood samples no more than 7 days prior to the scheduled health dialogue, where cholesterol levels and glucose levels are measured. Finally, the participants will arrive at their PCC for the scheduled health dialogue. The appointment will begin with an assessment of body weight, height, waist-to-hip ratio, and blood pressure. These data will then be incorporated, together with the blood sampling results and the survey data, into a risk profile assessment tool providing a visual result of the participant’s risk profile, known as the “Health Curve.” The risk profile displays a gradient in CVD risk ranging from green (low risk), yellow, to red (high risk) [14, 28]. Finally, the healthcare professional will use motivational interviewing techniques to perform an individually oriented, lifestyle-focused health dialogue guided by the risk profile. In total, the appointment is scheduled to take about 75–90 min including preparation time, the health dialogue, and administration. The actual dialogue is expected to take about 60 min, and for participants in need of an interpreter, an additional 30 min is expected. Notwithstanding the personalized health dialogue, detected risk factors for T2D and CVD (e.g., hypertension) will also be managed in accordance with existing care programs and clinical practice guidelines (https://viss.nu/). There are no criteria for discontinuing the intervention. There is no concomitant care that is prohibited during the trial.

#### Opportunistic screening (OS)

Patients consenting to participate in the trial, and enlisted at a PCC randomized to OS, will receive an intervention including screening for a smaller set of selected risk factors. The intervention will be conducted as follows. In conjunction with the participant’s scheduled appointment at the PCC, a screening is conducted by the healthcare professional with whom the patient has the appointment. The screening includes measurement of blood pressure, body weight, and height, and the patient is asked about tobacco usage. In total, the appointment is scheduled to take about 15 min. Thereafter, the patient is instructed to provide blood samples within 7 days, where cholesterol levels and glucose levels will be measured. Detected risk factors for T2D and CVD will be managed according to the existing care programs and clinical practice guidelines (https://viss.nu/), which should always include lifestyle advice as the first intervention. However, unlike the HDI, participants will not be offered an individually oriented health dialogue. There are no criteria for discontinuing the intervention and there is no concomitant care that is prohibited during the trial. Figure 3 presents a visual illustration of the core components of HDI and OS.

